### Unclassified Fever in Children

However, febrile illness is common in childhood, and is often due to viruses or other self-resolving illnesses [15,16]. In a large proportion of cases, fever resolves rapidly, almost always within 96 hours [17]. A number of studies have suggested that it is safe to withhold medical treatment for children with unclassified fever [18]. In Ethiopia, HEWs are instructed to follow the integrated management of neonatal and childhood illness (IMNCI) manual, which recommends that children seen by HEWs should only return for a re-assessment if the illness persists or deteriorates, that is, a *conditional* follow-up visit to the health post. However, HEWs and their supervisors report that a range of practices are applied for children with unclassified fever, including both conditional (as recommended) and universal follow-up advice, immediate referral to health centers, or treatment with antimalarial tablets, despite a negative malaria Rapid Diagnostic Test (mRDT).

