**Figure 2 figure2:**
[figure not shown]
Description of the 2 interventions arms, the current guidelines, and observed common practice. IMNCI: integrated management of neonatal and childhood illness.

At the day 3 re-assessment visit in the universal follow-up arm and at any spontaneous visit in both arms, the child will have a full re-assessment of their condition and the HEW will fill out a child assessment form. Caregivers will be asked whether the child remains febrile or whether the illness has resolved. If the child still has unclassified fever and a negative mRDT on re-assessment, the child will be referred to the nearest health center, as recommended in the national IMNCI guidelines. If the illness has resolved, the child will be sent home.

A clinically trained independent evaluator (IE) who is blinded to the study arm will visit all enrolled children at their home after 1 week to assess their clinical outcome. If caregivers report that the child is no longer ill and no fever is recorded, the child will be considered cured and no more follow-up will be done. If the caregiver reports that the child still has symptoms or if fever or other illness symptoms are detected during the assessment, the IE will follow the IMNCI algorithm and refer/treat the child accordingly. The IE will then follow-up again via a home visit after 2 weeks (day 15) and, if the child is still ill, on day 29.

At the day 8 visit, the IE will use a questionnaire to ask about individual and household characteristics, care-seeking and other treatments for the current illness episode, and reasons for returning/not returning to the HEW for follow-up care.

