### Data Analyses

The analysis of the primary outcome, treatment failure on day 8, will be done following a per-protocol approach. The baseline characteristics of the children and caregivers in both arms will be summarized using descriptive statistics. The difference between the percentage of the main study outcomes (persistent fever, persistent illness, or clinical deterioration [mortality, hospitalization, or danger signs], and these outcomes combined) of the 2 follow-up arms will be calculated. If the upper bound of the 95% CI of the difference in this percentage is less than 4%, the null hypothesis will be rejected; the conclusion will be that the conditional follow-up approach is not inferior to the standard approach. If there are imbalances in baseline characteristics across the 2 intervention arms, adjusted analyses of the difference in percentages will be conducted using multivariate logistic regression models.

The primary outcome will be compared between groups using generalized linear models with a binomial distribution and identity link using a robust variance estimator, treating cluster as a random effect. We will apply a conventional statistical noninferiority test using a CI approach using the exact binomial CI for the difference in overall treatment failure between intervention arms. The main analysis will be done using the per-protocol population (only including children for whom the primary outcome was collected on day 8±1 and whose caregiver reported receiving follow-up advice from the HEW that was aligned with the study arm), as is appropriate for noninferiority and equivalence studies, together with sensitivity analysis in the per-protocol and intention-to-treat populations [26]. Other descriptive statistics, such as cost of care seeking and compliance with the intervention protocol, will be compared between study arms using *t test* and chi-square statistics, respectively.

Qualitative interview transcripts from HEWs and caregivers will be coded and merged into sub-categories, categories, and themes using Nvivo (NVivo qualitative data analysis Software; QSR International Pty Ltd. Version 11, 2015). HEW interviews will be analyzed first and its results reviewed after caregiver interviews are read. For the purpose of this study, caregiver interviews will be analyzed and compared with main themes identified in the HEW interviews.

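### The noninferiority decision rests only on a per-protocol set selected by caregivers' post-randomisation report of advice; exclusions may depend on outcome and arm, and intention-to-treat does not govern the conclusion

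*Protocol article*

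**What the plan says.** Data Analyses opens with the choice of population: "The analysis of the primary outcome, treatment failure on day 8, will be done following a per-protocol approach". Two conditions define that set. The first is timing: "only including children for whom the primary outcome was collected on day 8±1". The second is the child "whose caregiver reported receiving follow-up advice from the HEW that was aligned with the study arm". The noninferiority criterion is an upper confidence bound below 4%. Other populations appear only as support: "together with sensitivity analysis in the per-protocol and intention-to-treat populations". The section gives no consequence if intention-to-treat and per-protocol disagree.

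The Interventions (text after Figure 2) describes the assessor at day 8: "A clinically trained independent evaluator (IE) who is blinded to the study arm". At the same visit this evaluator's questionnaire covers "care-seeking and other treatments for the current illness episode, and reasons for returning/not returning to the HEW for follow-up care".

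Unclassified Fever in Children says of practice before the trial: "HEWs and their supervisors report that a range of practices are applied for children with unclassified fever". These practices included both kinds of follow-up advice.

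**The concern.** Randomisation protects the comparison of all children by cluster allocation. It does not protect a subset chosen by something the caregiver says later. If the caregiver already knows whether the child recovered, and whether she went back, her account of the advice may be coloured by both. Aligned advice also means something different in each arm, so errors of recall need not balance. The excluded children could then differ in failure rate between arms, and the difference tested against 4% would no longer be the difference between the randomised groups.

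At stake is a safety conclusion intended to inform follow-up policy. If the two populations disagreed, the stated rule would follow the one without protection from randomisation. A loss of precision is added, because the enrolment target covers loss to follow-up but not exclusion for misaligned advice.

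**Working it through.** **Where the report could come from.** Data Collection limits the health extension worker (HEW) enrolment data to date, identifiers and clinical indicators. Return-visit forms exist only for children who come back, day 15 and 29 visits only for those still ill, and the semistructured interviews cover a subset. That leaves the evaluator's day 8 questionnaire as the only described caregiver interview for all enrolled children. Its listed content includes "reasons for returning/not returning to the HEW for follow-up care" but does not name the advice received. Collection at day 8 is thus a strong inference, not stated text. The order of questions and clinical assessment is not given.

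**Reproducing the plan's size.** Inputs from Sample Size: 5% universal, 6% conditional, margin 4 points, one-sided 5%, power 80%, design effect 3.

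- Variance term: 0.05×0.95 + 0.06×0.94 = 0.1039.
- n per arm before clustering: 0.1039 × (1.645 + 0.842)² / 0.03² = 713.7, rounded up to 714.
- With design effect: 714 × 3 = 2142 per arm, 4284 in total. This matches the plan.

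**Effect of selective exclusion at the margin.** Set the true rates among all children to 5% (universal) and 9% (conditional), so that declaring noninferiority is an error and should happen 5% of the time. If a share f of failures and g of recovered children is excluded, the rate left in an arm is

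p(1−f) / [p(1−f) + (1−p)(1−g)],

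and the bracket is the fraction of children kept. The error is Φ((4 − d)/SE − 1.645), where d is the remaining difference in points and SE uses the design effect of 3 with 2142 × (fraction kept) per arm. The 10% shares are assumptions; the protocol gives no misalignment rate.

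| 10% dropped among | Universal | Conditional | d (points) | SE (points) | Error |
|---|---|---|---|---|---|
| all children, both arms | 5.00% | 9.00% | 4.00 | 1.42 | 5.0% |
| recovered, conditional arm | 5.00% | 0.09/0.909 = 9.90% | 4.90 | 1.43 | 1.1% |
| recovered, both arms | 0.05/0.905 = 5.52% | 9.90% | 4.38 | 1.48 | 2.9% |
| recovered, universal arm | 5.52% | 9.00% | 3.48 | 1.40 | 10% |
| recovered universal and failed conditional | 5.52% | 0.081/0.991 = 8.17% | 2.65 | 1.37 | 26% |

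Similar exclusion totals would not reassure. If 20% of conditional-arm failures and 10% of everyone else are excluded, the totals are 10.0% (universal) and 10.9% (conditional), yet d is 3.08 points and the error 16.4%.

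**Effect on size.** 4900 × 0.90 = 4410 children with a day 8 outcome. 1 − 4284/4410 = 2.9% can be excluded before the target is missed. Power is Φ(3/SE − 1.645), with SE = 100 × √(3 × 0.1039/n) points:

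- 10% excluded: n = 2205 × 0.9 = 1984.5, SE 1.253, power 77%.
- 20% excluded: n = 2205 × 0.8 = 1764, SE 1.329, power 73%.

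**The case against.** Four arguments on the other side have weight.

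- **The filter suits the question.** A reader might infer that the usual reason for per-protocol in noninferiority is not met, because universal-arm children who skipped day 3 stay in. The documents do not support that. The intervention is the advice, both kinds were in use beforehand, and wrong-arm advice is a real source of dilution. Excluding non-attenders would tie membership to behaviour that may follow recovery. The rationale for a per-protocol analysis stands; what does not follow is that it should decide alone.
- **The direction is not established.** One might read the filter as producing false noninferiority. The table shows error below 5% as well as above it. Conditional-arm advice is itself to return if illness persists, so a caregiver of a failing child who says she was told to return need not be coded as misaligned.
- **Intention-to-treat is planned**, so a conclusion driven by exclusions could be exposed, and a rule for discordant results may stand in an analysis plan not shown. But the protocol itself names the main population and the criterion, and under these the sensitivity analysis decides nothing. Listing per-protocol among its own sensitivity analyses is only a wording point.
- **Blinding.** It is tempting to say that one interview unblinds a whole cluster. That is a risk, not a fact: given mixed prior practice, one caregiver's answers need not identify the arm. Death, hospitalization and measured temperature leave less room for judgement, and at least 10% of enrolled children and 50% of failures are re-assessed for quality control. The tension remains because the same evaluator both assesses the outcome and asks about return visits.

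**Conclusion.** The point holds as a risk that the stated rule leaves uncontrolled, not as a demonstrated bias. The decision depends on a post-randomisation, caregiver-reported criterion, apparently recorded when the outcome is known, and agreement with intention-to-treat is not required. With assumed 10% exclusions at 5% v 9%, a nominal 5% error becomes anything from about 1% to 26%, depending on who is dropped; exclusions unrelated to outcome leave it at 5%. These figures rest on a normal approximation, the plan's design effect of 3, and exclusion shares that the protocol does not document. The shortfall in size is firmer. Only 2.9% can be excluded for misaligned advice under the planned 10% loss, although the cost in power is modest (77% at 10% exclusion, 73% at 20%).

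**What to change.** Conclude noninferiority only if the upper bound is below 4% in both sets:

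- intention-to-treat: all enrolled children with a day 8 outcome, analysed by cluster allocation, with missing outcomes handled in a sensitivity analysis;
- per-protocol as now defined.

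Report the number excluded by arm and by day 8 outcome within arm. Restate power for the per-protocol set with an explicit assumption on misaligned advice. Qualify the statement that the evaluator is blinded, and report when and by whom the advice was recorded and whether this came before or after the clinical assessment.

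Enrolment was completed in 2016, so the order of questions can no longer be changed. The article describes analysis as under way, so the decision rule and the reporting still can be. Both analyses are already planned, and the cost is slightly lower power from requiring both.

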### Randomization

Cluster randomization will be at the health center level, corresponding to the lowest administrative unit where HEW services are coordinated; there will be 25 clusters in the 3 study woredas, with an average of 5 health posts and 7.5 HEWs per cluster. All clusters will be eligible for randomization. Restricted randomization will be performed to minimize the difference between intervention and control arms on key indicators, including average under-five population size, cluster distance to nearest zonal referral hospital, and number of unclassified fevers in children under 5 years seen by HEWs [23]. A validity matrix will be produced to confirm that no pairs are more or less likely to appear together than they would by chance. Sorting of clusters and random selection of schemes will be carried out in STATA 13 (STATA Corp, College Station, TX, USA).

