### Sample Size

The primary outcome on which sample size is based is the percentage of children with persistent fever, illness, or decline (hospital, danger signs develop, or death) at day 8. It is assumed that about 5% of children in both groups will still be ill at day 8 (based on rates of ~3% and 8% in previous studies [16,24]) and that this percentage will be approximately equivalent between groups. To calculate sample size, the outcome rate (ill at day 8) in the universal follow-up group is set to 5%, and it is assumed that the (true) corresponding outcome percentage in the conditional follow-up group will be no more than 6%. For the purpose of concluding that the conditional follow-up is noninferior to the universal follow-up approach, the upper bound of a one-sided 95% CI around the absolute difference in outcome rate (conditional minus universal) must not exceed 4% (noninferiority margin), assuming a power of 80% and an alpha of 5%. A design effect of 3 is used to account for clustering at HEW and health facility levels, generating a total sample size of 4284 children, with 2142 in each arm. To compensate for 10% loss to follow-up at day 8 and an additional 5% loss between day 8 and day 15, a total of 4900 children will be enrolled. Enrollment will occur over a period of 1 year to account for seasonality of various causes of febrile illness, starting in December 2015 and is expected to be completed around December 2016.

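### Cost of care seeking and compliance are compared between arms by an ordinary t test and chi-square, with no stated allowance for randomization by health center

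*Protocol article*

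**What the plan says.** The protocol article's Randomization section fixes the unit of allocation: "Cluster randomization will be at the health center level". Study Design gives 25 clusters, 13 in the universal arm and 12 in the conditional arm.

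The Sample Size section plans for dependence between children in the same unit: "A design effect of 3 is used to account for clustering at HEW and health facility levels".

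In Data Analyses, clustering is handled for one outcome by name: "The primary outcome will be compared between groups using generalized linear models with a binomial distribution and identity link using a robust variance estimator", with cluster entered as a random effect. The same paragraph then turns to other descriptive statistics, "such as cost of care seeking and compliance with the intervention protocol, will be compared between study arms using" a t test "and chi-square statistics, respectively". So cost gets the t test and compliance the chi-square. No cluster term, cluster summary or variance correction is mentioned for either.

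Data Collection shows that cost is recorded child by child at the home follow-up visits.

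**The concern.** An ordinary t test or chi-square treats every child as an independent observation. Here the independent units are 25 health centers. Children who share a center, and often the same HEW, are likely to resemble each other in what care costs them and in whether the advice was given and followed. If so, the difference between arms varies more than these tests assume, and chance differences between centers can pass as effects of the follow-up advice.

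The article names the tests, so this is a stated method that does not fit the design and not a detail left to an analysis plan. What is at stake is limited to the between-arm statements on cost and compliance. They have some weight: the Introduction raises burden on families and HEWs, and asks which advice would be better complied with.

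**Working it through.** **Inputs from the protocol article**
- Sample Size: failure 5% (universal) and 6% (conditional), margin 4%, one-sided alpha 5%, power 80%, design effect 3, total 4284.
- Study Design: 25 clusters, 13 and 12.

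**Inputs assumed**
- The design effect for cost and for compliance. The documents give none, so a range is shown.

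**1. Reproduce the plan's sample size, the source of the design effect.**
Per arm before clustering: (1.645 + 0.842)² × (0.05 × 0.95 + 0.06 × 0.94) / (0.04 − 0.01)² = 713.7, rounded up to 714. Times 3 gives 2142 per arm, and 4284 in total. This matches the article exactly.

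**2. Intracluster correlation implied by a design effect of 3, if all of it sits at health-center level.**
Children per center: 4284 / 25 = 171.4. ICC = (3 − 1) / (171.4 − 1) = 0.0117. A small correlation is therefore enough.

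**3. True size of an unadjusted nominal two-sided 5% test.**
If the real variance of the difference is DE times the assumed variance, the rejection rate under no difference is 2 × [1 − Φ(1.96 / √DE)].

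| Design effect | False-positive rate |
|---|---|
| 1 | 5.0% |
| 1.5 | 11.0% |
| 2 | 16.6% |
| 3 | 25.8% |
| 4 | 32.7% |
| 5 | 38.1% |

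At a design effect of 3, the unadjusted 95% interval has 1/√3 = 58% of the proper width.

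**4. Check by simulation** (20,000 runs, 13 versus 12 clusters of 171 children, no true difference, ICC about 0.012).
- With equal clusters, the t test rejected in 25.5% of runs and the chi-square in 25.8% (true proportion 0.5) and 26.7% (0.8).
- With unequal clusters (assumed coefficient of variation of size 0.5), the rates were 28.6% for the t test and 29.1% for the chi-square.
- In a separate simulation with equal clusters, a t test on the 25 cluster proportions rejected in 4.8% to 5.2% of runs.

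**5. If fewer children contribute cost data** (assumed; for example, only those who sought care), keeping ICC 0.0117:
- 50 per center: DE = 1 + 49 × 0.0117 = 1.57, rate about 12%.
- 20 per center: DE = 1 + 19 × 0.0117 = 1.22, rate about 8%.

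**6. If clustering is stronger** (assumed), with 171.4 children per center:
- ICC 0.02: DE = 1 + 170.4 × 0.02 = 4.4, rate 35%.
- ICC 0.05: DE = 9.5, rate 53%.

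**The case against.** Several counter-arguments have force.

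- **The design effect belongs to another outcome.** It was chosen to size day 8 treatment failure. A reader might infer that the protocol itself implies a false-positive rate of about 26% for cost and compliance. It does not, because it gives no design effect or ICC for either. This stands, so the figure is illustrative.
- **The unit of analysis is not stated.** A t test on center means would be valid. However, no center summary is described, and a chi-square for compliance works on counts of children. The individual-child reading is the natural one, but it remains an inference.
- **The simulation simplifies the design.** The article attributes clustering to both HEW and facility levels, and the restricted randomization balances distance to the referral hospital, which may predict cost. The split between levels does not change step 3, which uses only the total inflation. Restriction could lower the rate for cost. Higher ICCs or unequal centers would raise it.
- **These are descriptive items.** The article calls them so, cost is not a listed secondary outcome, and no decision rule is attached. That limits the importance, but the sentence still prescribes between-arm tests, and the label does not make them valid.
- **The trial's question is safety.** A reader might infer that the case for conditional follow-up rests on cost and compliance. The aim, the primary objective and the decision rule concern clinical deterioration only. Burden and compliance appear as background.

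**Conclusion.** Wrong as written, of minor to moderate severity. The article names ordinary tests for two between-arm comparisons in a trial that randomizes 25 health centers, and it provides for clustering only in the primary outcome model. Applied to individual children, these tests give standard errors that are too small whenever outcomes correlate within centers.

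The direction is firm; the size is not. It is about 26% instead of 5% if the design effect of 3 carries over, with an assumed range of about 17% (design effect 2) to 38% (design effect 5), and about 8% to 12% if only 20 to 50 children per center contribute. The tests would hold their level only with a design effect near 1.

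A reader might infer that the noninferiority result is also compromised. This point does not support that: the affected sentence concerns other variables and other tests. Only the statements comparing cost and compliance between arms are affected.

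**What to change.** Replace the sentence so that any between-arm test of cost or compliance respects the health center. Two suitable choices are:
- a t test on the 25 health-center means (cost) or proportions (compliance), with 13 + 12 − 2 = 23 degrees of freedom;
- a mixed or GEE model by health center with a small-sample correction.

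Report the difference with its cluster-adjusted confidence interval. If no inference is wanted, present the figures by arm without between-arm p values.

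The cost is one sentence and slightly different code, with no new data or participants. The article says that analysis was still under way, so the change was feasible at publication. The downside is wider intervals: about √3 = 1.7 times as wide at a design effect of 3, and less if clustering is weaker. That extra width is the uncertainty that the unadjusted tests leave out.

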### Ethics Approval and Consent to Participate

The trial protocol was approved by the SNNPR State Health Bureau on September 23, 2015 (ref P026-19/4511). In addition, approval was obtained from the district authorities and local leaders in the woredas where the study is being conducted. Co-investigators from Centers for Disease Control and Prevention participated under a nonengaged determination from their Human Research Protection Office.

Each caregiver whose child is eligible for enrollment is provided with a sheet containing information about the study in Amharic. Caregivers are given time to read the information sheet, and the HEW verbally summarizes key points and answers any questions. Agreement to participate is indicated by signature or thumb print. The individual’s right to refuse consent or to stop the interview at any time after consent has been given is preserved.

The project has a 3-person Data Monitoring Committee (DMC) with external members having expertise in child health, epidemiology, iCCM, and randomized controlled trials. The DMC is responsible for safeguarding the interests of study participants, assessing the safety of the intervention during the trial, and for monitoring the overall conduct of the study. The DMC provides recommendations about stopping or continuing the study and other aspects of trial implementation, using interim data analysis reports on cluster-specific enrollment rates, adherence to follow-up recommendations, and on characteristics of the children and households enrolled.

The DMC is advisory to the study Steering Committee, which comprises the lead study investigators, who are jointly responsible for the design, conduct, and analysis of the trial. The Steering Committee is responsible for promptly reviewing the DMC recommendations, to decide whether to continue or terminate the study, and to determine whether amendments to the protocol or changes in study conduct are required.

